**Acceptability of the intervention:** **Assessed via:**		
Was the intervention acceptable to health visitors and key stakeholders?	a) Interviews with health visiting teams members, health visiting team leads, and local authority leads for oral health	FDS was acceptable to stakeholders, HVTs, and parents, based on interview feedback.
Was the intervention acceptable to parents?	a) Interviews with parents	

### Secondary outcomes

These secondary outcomes are the anticipated primary outcomes for a future randomised controlled trial of the First Dental Steps intervention. These outcomes include oral health behaviours such as tooth brushing frequency, toothpaste use, diet (specifically sugar consumption), and self-reported dental check-ups. In this study, these oral health behaviours will be collected at two time points, using a pre-structured, self-complete questionnaire completed during the 12-month mandated check (baseline) and approximately 5 months later (follow-up).

An economic evaluation will not be conducted in this study. However, we will explore the opportunities and methods for resource use (healthcare staff time, facilities, or consumables) data collection in order to estimate intervention costs and consequences, in a future trial.

### Participants

Vulnerable families (within the intervention local authority areas) will be identified and invited to participate in the intervention and the feasibility study by the health visiting team. As a result of resource constraints study documents will not be translated into different languages, however, as health visitors will be recruiting the families and helping the families complete the consent form and questionnaire, non-English speaking families may be included if the health visitor is able to communicate with them. For the purposes of this study, we define vulnerable families as those who have been identified as needing additional support from the health visiting team (Universal Plus), or multiagency support (Universal Partnership Plus). Only families that provide consent to be involved in the research will be included. As part of the research, we will also invite families to participate in a telephone interview. This interview is an additional step and families can decline to participate. The family can still however complete the baseline and follow-up survey, thus remaining involved in the study. No other inclusion or exclusion criteria will be applied to the recruitment of families.

The study population will be families that meet the inclusion criteria and all eligible families will be invited to participate by the health visiting teams. In total, the five health visiting teams estimated that they may see as many as 789 families during the 6-month study period (01 June 2021 to 31 January 2022).

Qualitative interviews will be undertaken with all agreeing key stakeholders (Local Authority Oral Health Leads and Health Visiting Team Leads) across all the included intervention and comparison local authority areas. Additionally, in the intervention sites, the health visitors who received the training and were involved in the delivery of the intervention and research will also be invited to participate in an interview. We will also invite consenting families to participate in an interview, additional consent will be obtained for these interviews at the time that the family completes the initial consent. At the start of the interview, participants will be asked to verbally confirm their consent. No further inclusion or exclusion criteria will be applied.

A purposive sample of health visiting team members, working in the five intervention local authority areas will be interviewed. A further, purposive sample of key stakeholders including the providers of the oral health training, health visiting team leads, and local authority leads for oral health will also be interviewed. These samples will be selected to ensure representativeness across the different local authorities, health visiting teams, gender, and differing levels of experience or leadership.

A purposively selected sample of parents, who provide consent for the interview will be contacted. The sample will be drawn from the different sites, gender, and ethnic groups to ensure representativeness.

Recruitment for all these interviews will continue until data saturation is reached but it is anticipated that 15–20 interviews will be required for each group (health visiting team members, stakeholders, and parents).

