## Methods and design

### Intervention description

The First Dental Steps intervention includes a universal and targeted element, the targeted element is being assessed in this study. The universal element includes offering oral health training for the health visiting teams involved in 0–5 years, preparing them to provide families with evidence-based advice on oral health diet, oral health, and oral hygiene, when to attend the dentist, and signposting to dental services. The training material is based on the ‘NICE Public Health Guidelines [PH55] Oral Health: local authorities and partners’ [14] as well as the ‘PHE Delivering better oral health: an evidence-based toolkit for prevention’ [16]. The learning objectives and workshop programme are provided in Supplementary file 1. The training was delivered in 2-h sessions which were delivered between January 2019 and January 2020. This training was primarily focussed on health education rather than behaviour change.

The targeted element of the First Dental Steps intervention will be delivered to vulnerable families, receiving their 1-year mandated check. There are three components to this element of the intervention including providing families with evidence based oral health care advice and information and an oral health pack. Further, children in these families that are at increased risk of dental caries, identified by having an older sibling that has had teeth extracted under general anaesthetic, will also be referred to local community dental care services for specialist preventative advice and treatment, where the required pathways are in place. The oral health pack includes a free flow cup, an age-appropriate toothbrush, and 1450 ppm fluoride toothpaste.

The health visitors were not given any materials (printed or demonstration items) to take with them into the home visit. Based on their training the HVs were instructed to construct advice for the parents that covered; encouraging them to start brushing their child’s teeth with fluoride toothpaste, advice around diet, and transitioning from baby-bottles or “sucky” beakers. HVs also provided families with details for local dental services, where possible. All of the above was tailored by the HVs to the individual needs of each family, for example some families may have needed more support around encouragement to brush, while others required more information around diet.

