	*Procedures: Describe each of the procedures, activities, and/or processes used in the intervention, including any enabling or support activities*	First Dental Steps includes a universal and targeted element, the targeted element is being assessed in this study. Universal element: The universal element includes offering oral health training delivered to health visitors or community nursery nurses preparing the attendees to be “Oral Health Champions”. The training aims to enhance their ability and confidence to provide families with evidence-based oral health advice on diet, oral health, and oral hygiene, when to attend the dentist, and signposting to dental services. Targeted elements: Under the current health visiting model, health visiting services offer services on four levels, with Universal Plus and Universal Partnership Plus, being the final two offered to the more vulnerable families. Universal Plus offers rapid response from the local health visiting team when specific expert help is needed. While Universal Partnership Plus, a level provided for the most vulnerable families, delivers ongoing support from health visiting teams and a range of local services (usually social care and other partners) to address more complex issues over a period of time. The targeted element of the First Dental Steps intervention will be for families receiving the Universal Plus or Universal Partnership Plus tier of the HV service. Oral Health Champion trained health visitors will distribute packs (described above) to these vulnerable families. Where possible they will also, set up a direct referral pathway for children identified as being at high risk of developing tooth decay to the local Community Dental Services where they can access specialist preventative advice and treatment.
**Who provides**	*For each category of intervention provider (such as psychologist, nursing assistant), describe their expertise, background, and any specific training given*	The First Dental Steps intervention will be delivered by health visiting team members who will receive additional training on being an Oral Health Champion (described above).

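### Parent interviews are sampled by site, gender and ethnic group, but not by the service tier that defines the target population or by the sibling-extraction marker that triggers referral

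*Protocol article*

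**What the plan says.** The Participants section of the protocol article sets out the parent sample. "A purposively selected sample of parents, who provide consent for the interview will be contacted", and "The sample will be drawn from the different sites, gender, and ethnic groups", with representativeness as the stated aim. Recruitment runs to data saturation, and "it is anticipated that 15–20 interviews will be required for each group". Agreeing to be interviewed is optional for families in the study.

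The same section defines eligible families as those "needing additional support from the health visiting team (Universal Plus), or multiagency support (Universal Partnership Plus"). Table 2 (Procedures) describes "Universal Partnership Plus, a level provided for the most vulnerable families".

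The Intervention description gives the targeted element three components: advice, the oral health pack and, for some children, referral to community dental care. Referral is for children at increased risk, "identified by having an older sibling that has had teeth extracted under general anaesthetic", and only where a local pathway exists.

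Table 3 makes acceptability a progression criterion: "FDS was acceptable to stakeholders, HVTs, and parents, based on interview feedback". It sets no threshold and does not say which kinds of parent must be heard.

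Table 4, the participant flow table, has a row for tier and a row for the sibling-extraction marker, both against the unique ID.

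**The concern.** A purposive sample is only as informative as the characteristics used to choose it. The parent frame covers place, gender and ethnicity. It omits the characteristic that decides who is offered the targeted element and separates the most vulnerable families from the rest. It also omits the marker that separates families eligible for all three components from those eligible for two. The staff and stakeholder frame in the same section does include a role-specific characteristic, the level of experience or leadership. The parent frame has no counterpart.

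The conclusion that parents found the intervention acceptable feeds the decision on a future trial in the same families. If few of the interviewed parents come from the higher tier, or none has the referral trigger, that conclusion could be read more broadly than the sample supports. Nothing in the stated frame would reveal it. Saturation among the parents who were sampled does not show that a group left out was heard.

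**Working it through.** **No figure to reproduce.** The 15–20 interviews are a qualitative expectation tied to saturation, with no formula behind them. The question is how often a frame that ignores tier and the referral trigger would yield little or nothing from a subgroup.

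**Inputs**
- Number of parent interviews, k = 15 or 20 (Participants).
- Subgroup share among interview volunteers, s. The document does not give it, so s is assumed and varied from 5% to 30%.
- Selection is taken as unrelated to tier and to the trigger.

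**Formulas**
- Chance of none: P(0) = (1 − s)^k.
- Chance of two or fewer: P(≤2) = (1 − s)^k + k·s·(1 − s)^(k−1) + [k(k−1)/2]·s²·(1 − s)^(k−2).

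**Worked example, s = 20%**
- k = 15: 0.0352 + 0.1319 + 0.2309 = 0.398.
- k = 20: 0.0115 + 0.0576 + 0.1369 = 0.206.

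| Assumed share s | P(none), k = 15 / 20 | P(two or fewer), k = 15 / 20 |
|---|---|---|
| 5% | 46% / 36% | 96% / 92% |
| 10% | 21% / 12% | 82% / 68% |
| 15% | 9% / 4% | 60% / 40% |
| 20% | 3.5% / 1.2% | 40% / 21% |
| 30% | 0.5% / 0.1% | 13% / 4% |

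**Share needed for P(none) to be 5% or less:** s = 1 − 0.05^(1/k), which is 18.1% for k = 15 and 13.9% for k = 20.

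**Finite-pool check.** The Participants section expects up to 789 families, and Table 3 asks for at least 30% consent. 0.30 × 789 = 236.7, or about 237. Drawing without replacement from 237 gives, at a 10% share, 19% / 11% for none. At a 20% share it gives 40% / 20% for two or fewer. The results barely move. Interview volunteers would be fewer than 237, which would lower the chance of none a little further.

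**Which rows apply to which group.** Universal Partnership Plus is one of only two eligible tiers, so the lower rows may suit it better. Families with the referral trigger are a subset defined by a sibling's history, so the upper rows are the more natural guide. Both placements are judgement, because the document gives no shares.

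**The case against.** The strongest reply is that nothing here contradicts the plan. Every eligible family is in one of the two vulnerable tiers, so the sample cannot miss the target population. The stated aim is already representativeness, sampling is purposive and not random, and interviews continue to saturation. A detailed sampling matrix may also sit in a fuller protocol. All of this stands, and it makes the point an improvement and not an error. It does not remove the point, because the article itself names the parent sampling variables and tier is not among them.

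A reader might infer four stronger things that the document does not support.
- *The most vulnerable tier is likely to be missed altogether.* At a share of about 20% or more, no interviews from that tier is unlikely unless these families volunteer less often. The plan does not guard against that, but gives no evidence of it either.
- *Tier and referral vary within every site.* Referral is limited to places with a pathway, so sampling by site covers part of it. How tier is distributed within sites is not stated.
- *Referral status is already recorded.* The Table 4 text shown records the trigger, a sibling's extractions. It does not record whether a referral was made.
- *The change is free.* The flow table is returned to the researchers anonymously (Table 2, fidelity), and contact details are held apart from questionnaire data (Data management). Some linkage must be built before tier can guide the choice of interviewees.

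Sampling on the trigger also has limited reach. Parent interviews take place shortly after baseline and may precede any dental appointment, and referral is not among the parent topics listed under Data collection and instruments.

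**Conclusion.** The point holds as a low-cost improvement. The parent frame leaves out service tier, which defines the target population, while parent acceptability is judged on interview feedback alone. It also leaves out the marker that triggers referral.

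For Universal Partnership Plus the realistic risk is few interviews: two or fewer has a 40% / 21% chance with 15 / 20 interviews at a 20% share, and more at lower shares. None is unlikely from about 20% upward. For a rarer group, such as families with the referral trigger, none is a real possibility: 46% / 36% at 5% and 21% / 12% at 10%.

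These figures rest on assumed shares and on selection unrelated to tier or trigger. Purposive selection with an informal eye to tier would lower them, and lower volunteering among the most vulnerable families would raise them.

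**What to change.** 1. In the Participants section, add service tier to the parent sampling variables. Add the Table 4 sibling-extraction marker too, where such families volunteer and a local referral pathway exists. Aim for several parents from each tier, without rigid quotas.
2. Before tier is used, reconcile its label in Table 4 with the tier names elsewhere. Table 4 calls the lower tier Universal Partnership, whereas Table 2 and the Participants section call it Universal Plus.
3. Carry the unique ID or the tier onto the linked interview-consent form, so that selection can use it.
4. Report the interviewed parents by tier and by the referral trigger beside the acceptability conclusion. Call it the trigger and not referral status. Note that interviews shortly after baseline can speak to the offer of referral but perhaps not to its receipt.

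The cost is a small change to one form and slightly slower selection of interviewees. Both items are already rows in Table 4, so families would not have to be asked anything new.

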### Public involvement and engagement

A dedicated public involvement and engagement group, including primarily parents of young children will be consulted in relation to the usability and understandability of both the baseline and follow-up questionnaires. This group will also be consulted on the interview topic guide and resource use questionnaire.

### Process

Eligible families will be invited to participate at the point of their 12-month mandated check by the health visiting team. The family will be informed of the steps involved in the research, including the initial questionnaire (baseline), the follow-up questionnaire and an optional telephone interview. Participation is completely voluntary and participants can withdraw at any point without giving a reason. If they are interested in participating in the study the health visiting team will either assist the family with completing a digital or paper-based consent form and the subsequent baseline questionnaire or provide the family with a weblink to complete these independently at a later date. All vulnerable families within the participating local authorities will be provided with the intervention as part of their mandated check. Families provide consent to participate in the research only. Recruitment will take place over a period of 5 months. All participants will be given a copy of their signed consent form, and this will either be a downloadable electronic copy or a paper copy.

For the intervention, data will be collected at two time points; first at the 12-month mandated check (referred to as baseline), and at follow up, approximately 5 months later. A study overview is shown in Fig. 2.

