**How**	*Describe the modes of delivery (such as face to face or by some other mechanism, such as internet or telephone) of the intervention and whether it was provided individually or in a group*	The targeted element of the First Dental Steps intervention will be delivered individually to the vulnerable families by the trained health visiting teams. In some local authorities this will be delivered face-to-face, while in others this will be carried out over video conferencing or telephone call. In these situations, the oral health packs will be delivered to the family either by drop-off from a member of the health visiting team or via a collection point or postage.
**Where**	*Describe the type(s) of location(s) where the intervention occurred, including any necessary infrastructure or relevant features*	For both the universal and targeted elements of First Dental Steps, the intervention will take place as part of the professional’s normal operating, as such, some level of advice or sign posting may occur telephonically or remotely. However, for the targeted element, the First Dental Steps intervention will also occur as part of the health visiting team’s mandated checks with vulnerable families, these checks will likely take place in the family home or in established clinics. No additional infrastructure is required.
**When and how much**	*Describe the number of times the intervention was delivered and over what period of time including the number of sessions, their schedule, and their duration, intensity, or dose*	The health visiting team training workshops will take place prior to the study period. The oral health advice and distribution of oral health packs will take place as part of the 12-month mandated check, during a 5-month period. Each child will receive only one pack during the study period. However, families may be in contact with health visiting teams more than once during the study period and may receive additional advice, information, or signposting during the study period.
**Tailoring**	*If the intervention was planned to be personalised, titrated or adapted, then describe what, why, when, and how*	Nothing planned
**Modifications**	*If the intervention was modified during the course of the study, describe the changes (what, why, when, and how)*	The research team will document this throughout the study and report, as need be, with the results.

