### Design and setting

This feasibility study is a non-randomised, pre-post, observation study which follows the 2013 Medical Research Council Guidance for Complex Interventions on conducting a feasibility study prior to conducting a full trial [18], which covers testing procedures, recruitment, and retention.

The study will be based in the South West region of England. The study will be delivered through the health visiting teams which are commissioned at the local authority level. Six local authorities in the South West will be chosen by Public Health England to take part in the intervention. Five of these will be selected for this feasibility study to keep the study manageable within the budget, and also do not have any planned service changes during the study period. Intervention sites will aim to deliver the intervention for 1 month before recruitment begins.

A further four comparison local authorities will be invited to take part. These will be identified from the same region but who were not selected to take part in the First Dental Steps intervention and do not have any other commissioned child oral health interventions at the time. The comparison sites will only be invited to take part in stakeholder interviews, these will be with local authority oral health leads and health visiting team leads.

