### Data collection and instruments

Baseline and follow-up questionnaire data will be collected using a pre-structured, self-completed digital questionnaire, completed with the assistance of the health visiting team members where possible. The questionnaire is based on three existing validated measures and was tailored for this study with support of a patient and public involvement group. The National Children's Dental Health Survey, 2013 (parent and child questionnaires) [20], these questionnaires were developed by stakeholder consultation, and they underwent expert review, cognitive testing, pilot testing, and ethical review [21]. Additionally, the Born in Bradford: 12 months questionnaire [22], a questionnaire originally based on validated measures and any bespoke questions were tested within their sample and modified accordingly [23]. Finally, the Strong Teeth study questionnaire [24], a questionnaire based on validated measures, was also consulted [24]. We then tailored our questionnaire with support of a patient and public involvement group. The questionnaire is two pages long, with nine questions, and should take no more than 10 min to complete. The key areas that the questionnaire covers are current tooth brushing frequency, diet, and dental check-ups. Demographic details such as the age of the child, relationship of the parent, guardian, or carer of the child that is completing the questionnaire, socio-economic status, ethnicity, and if the child has any older siblings are also included. Our questionnaire was developed to include items from existing measures, however, there is limited data on the reliability of the use of self-report oral health or hygiene practices, with some previous research exploring this among adolescents in Brazil [25].

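### The baseline questionnaire may be completed by weblink after the check at which advice is given, which contradicts the stated baseline timing and can shrink the exploratory pre-post change in tooth brushing

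*Protocol article*

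**What the plan says.** Design and setting describes the design: "This feasibility study is a non-randomised, pre-post, observation study". Comparison areas contribute stakeholder interviews only, so families are surveyed in intervention areas alone. Objective 5 is to explore a possible effect on tooth brushing.

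The intervention is tied to one visit. Table 2 (When and how much) states: "The oral health advice and distribution of oral health packs will take place as part of the 12-month mandated check". Process adds: "All vulnerable families within the participating local authorities will be provided with the intervention as part of their mandated check".

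The baseline is tied to the same visit in two places. Secondary outcomes has the behaviours collected "using a pre-structured, self-complete questionnaire completed during the 12-month mandated check (baseline", and again about 5 months later. Process gives the two time points as "first at the 12-month mandated check (referred to as baseline), and at follow up, approximately 5 months later".

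Process also offers a second route. If the family does not complete consent and baseline with the team's help, the team may "provide the family with a weblink to complete these independently at a later date". No time limit is given.

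On content, Data collection and instruments says: "The key areas that the questionnaire covers are current tooth brushing frequency, diet, and dental check-ups". Table 4 records the date of the baseline questionnaire and, if possible, a rough time. It records whether and how the pack was given, but no date for the pack or the advice.

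**The concern.** A pre-post comparison needs a first measurement that the intervention has not touched. Families are first invited at the visit that delivers the advice, so no earlier contact supplies one. A weblink answer given days later comes after the advice, and often after the toothbrush and toothpaste have arrived. If it describes current brushing, it may describe behaviour that has already begun to change.

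Within a visit, the text shown does not say whether the questionnaire or the advice comes first. A parent who has just been advised to brush may overstate current brushing.

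At stake is objective 5. With no families surveyed in comparison areas, baseline against follow-up is its only contrast. Secondary outcomes also names these behaviours as the anticipated primary outcomes of a future trial, so the way baseline is collected is itself being piloted.

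**Working it through.** The plan states no figure to reproduce. The check sets the timings side by side and then asks how large the distortion could be.

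**Timings**

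| Event | When | Where stated |
|---|---|---|
| Invitation | At the 12-month check | Process |
| Advice | At the 12-month check | Table 2; Process |
| Pack | At the check; by drop-off, collection point or post where the check is remote | Table 2 (How; When and how much) |
| Baseline, route 1 | During or at the check | Secondary outcomes; Process |
| Baseline, route 2 | Later, alone, by weblink | Process |

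1. Route 2 contradicts the timing given in Secondary outcomes and the timing that Process itself gives.
2. Under route 2 the advice comes before the baseline. The pack may come before or after it when it is posted, dropped off or collected.
3. Under route 1 the order is open. Table 4 lists the pack above consent and baseline, but the order of rows on a form does not prove the order of events.

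**Size of the distortion under route 2**

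Let p be the true pre-advice brushing level, D the true change by follow-up, f the share of baselines taken late, and g the fraction of D already present when a late baseline is taken. Assume that late and on-time families have the same p and D, and that follow-up is unaffected.

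- Mean recorded baseline = (1 - f) × p + f × (p + g × D) = p + f × g × D
- Observed change = (p + D) - (p + f × g × D) = D × (1 - f × g)

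The documents give none of f, g or D. For illustration only, take D = 15 percentage points in twice-daily brushing:

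| f | g = 0.25 | g = 0.5 | g = 1 |
|---|---|---|---|
| 0.2 | 95%, 14.25 points | 90%, 13.5 points | 80%, 12 points |
| 0.4 | 90%, 13.5 points | 80%, 12 points | 60%, 9 points |
| 0.6 | 85%, 12.75 points | 70%, 10.5 points | 40%, 6 points |

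For example, with f = 0.6 and g = 1: 1 - 0.6 × 1 = 0.40, and 15 × 0.40 = 6.

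**Can affected baselines be found?** Table 4 dates the questionnaire but not the advice. Table 2 (How well) says that teams record each appointment electronically and are asked to record delivery of advice and pack there. If those records are dated, which is not stated, comparing the dates would reveal baselines completed on a later day. The order within one visit is not recorded in either place.

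**The case against.** The strongest reply is that little depends on this comparison. Objective 5 only explores a possible effect, and the behaviours are secondary outcomes. The two numerical progression criteria in Table 3 (at least 30% consent, no more than 30% loss to follow-up) do not use brushing data, and neither does any other criterion there. An uncontrolled change over 5 months in one-year-olds could not be read as an effect even with a perfect baseline. All of this stands and limits the severity.

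A reader might infer more than the documents support in four ways:

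- **That the study has no pre-intervention measure at all.** A family answering at the visit, even just after the advice, reports brushing that cannot yet have changed. The risk there is desirability bias. Only the later route risks recording changed behaviour, and assistance by the team is planned where possible, so that route may be the minority one.
- **That late baselines cannot be identified.** Health visitor records may allow this for later-day answers. Only the order within a visit is lost.
- **That the change would shrink to 12, 9 or 6 points.** Those figures need the whole effect to be present already in every late responder (g = 1), which is the worst case.
- **That late baselines should be prevented or excluded.** Compulsory consent and baseline before advice, or a link sent with the appointment, could alter the consent rate that the study is testing. Exclusion could selectively drop remote or less engaged families.

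Fig. 2 and the questionnaire are not shown. The figure might set an order within the visit, and the items might already have a reference period. Neither would remove the written weblink route or the contradiction over timing.

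**Conclusion.** The point holds as an inconsistency with a limited consequence. The article fixes baseline at the check in two places and lets it move to an unspecified later date in a third. It does not place the questionnaire before the advice in the text shown.

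Late answers can reduce the observed brushing change to between 95% and 40% of the true change under the assumed ranges of f and g. The direction follows from the arithmetic as long as some of the effect is already present. The size is unknown. Desirability bias in answers given at the visit after advice would also raise the recorded baseline. Its net effect on the change is not determined, because follow-up answers may be given on a call and could be inflated too.

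The feasibility, acceptability, consent and retention conclusions are unaffected. This should be fixed, but it does not undermine the study's main purpose.

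**What to change.** 1. Reconcile Secondary outcomes with Process, so that both describe the same baseline timing and both mention the weblink route.
2. When the questionnaire is completed at the check, have it done before the oral health advice.
3. Keep the weblink, but word the baseline behaviour items to refer to the period before the check, for example the week before.
4. Add to Table 4 the date of advice, the date the pack was received, whether baseline came before or after the advice, and whether the health visitor assisted (yes/no).
5. Report the objective 5 change separately for baselines taken before and after the advice. Make the pre-advice group the main result and show all families alongside.

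The cost is small: a few extra fields for the teams, some recall error among late responders, and a smaller main comparison for objective 5. Because the weblink stays and no family is excluded from the study, the recruitment route under test is kept.
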